#### Cognitive Behavioural Therapy (CBT)

CBT will be focused on the perpetuating factors of fatigue as established in previous research [10,12,24] and based on experience in clinical practice. These factors encompass insufficient coping with the disease, dysfunctional illness cognitions, catastrophizing, deregulation of sleep, deregulation of activity, low social support and negative social interactions (see appendix 1 for the various modules). Because of large inter-individual differences, CBT will be adapted to the needs of each patient. For instance, barriers to become more physically active are explored and possibly alleviated in some patients, whereas overactivity is reduced in others. To determine which modules are appropriate, each perpetuating factor is assessed with specific tests, and within each module, the CBT approach is standardized (see appendix 1). The precise number of sessions is dependent on the number of modules. Each session has a duration of one hour and is given at the most nearby participating centre by a registered cognitive behavioural therapist, especially trained in CBT for FSHD. The therapists have been specifically trained to use the diagnostic tests and indicate the different modules and are regularly supervised by one of the investigators (GB).

#### Compliance and attrition

Therapy compliance is assessed by recording the number of treatment sessions (AET and CBT). For the participants randomized to AET, the total time spent on the bicycle ergometer at home is recorded as well. When applicable, participants are asked for their reasons for poor compliance. In the case of therapy drop out, patients are asked for the reason of non compliance and are stimulated to continue participation in the assessments until the last follow-up.

#### Outcome assessment

Outcome measures are listed in table 2. The primary outcome measure is fatigue severity as assessed with the CIS-fatigue [21]. Secondary outcome measures are categorized according to the different ICF levels [25]. Outcome measurements are obtained at the Radboud University Nijmegen Medical Centre at the start of the study period (T0), immediately after the intervention period of 16 weeks (T1) and after 3 (T2) and 6 months of follow-up (T3). Observers of the secondary outcome measurements are experienced physical therapists blinded for treatment allocation. At the first measurement (T0), demographic data is obtained by the primary investigator and physician (NV), as well as a general and FSHD related medical history, anthropometric measures (diastolic and systolic blood pressure in mm, resting pulse rate in beats per minute and auscultation of heart and lungs), to verify eligibility. The baseline (T0) and post treatment (T1) visits consist of muscle strength testing of the thigh and aerobic exercise tolerance testing. Participants are asked to complete the questionnaires and to wear the actometer for 12 consecutive days. An actometer is a motion sensing device that can register and quantify human physical activity and has to be worn at the ankle [26,27]. Blood and urine analyses and MRI, MRS and ultrasound measurements of the thigh muscles are performed. Follow-up measurements (T2 and T3) consist of muscle strength testing of the thigh, aerobic exercise tolerance testing, questionnaires are completed and the actometer is provided.

**Table 2 T2:** Outcome measures and tests

	Tests
**Primary outcome measure**	

Fatigue severity	Checklist Individual Strength (CIS subscale fatigue) [30]

**Secondary outcome measures**	

***ICF: bodily funtions***	
Aerobic exercise tolerance	Maximal oxygen consumption (VO2 max) using the Astrand protocol[31]
	6-minutes walking test [32]
	Resting heart rate
Muscle strength of quadriceps,	Quantitative Muscle Assessment using fixed myometry testing
hamstrings and tibialis anterior	system (QMA) [18]
muscles	
Cardiovascular risk factors	Blood pressure*
	Abdominal circumference
	Weight/Body Mass Index (BMI)
	Percentage body fat
	Visual Analogue Scale (VAS) [33]
Pain	Daily Observed Pain (during a period of 2 weeks) [27,34]
Psychological well-being and	Brief Symptom Inventory (BSI) [35]
sleeping pattern	
Metabolic biomarkers	Blood and urine analyses for creatine, glucose, creatine kinase,
	sodium, potassium, calcium, phosphorus, ureum, ALAT, ASAT,
	gamma-GT, bilirubine, AF and LDH***
Structural and metabolic muscle characteristics	T1 MRI, T2 MRI, ^31^P and ^1^H MRS analysis of muscle specific creatine, extramyocellular lipids, intramyocellular lipids, levels and phosphometabolites in thigh muscles; ultrasound of thigh muscles

***ICF: activities***	
Physical activity in daily life	Actometer, a motion sensing device (during a period of 2 weeks)
	[26,27]
	Daily Observed Spontaneous physical activity (during a period of 2 weeks) [27,34].
	Checklist Individual Strength (CIS subscale physical activity) [30]
Self perceived functional status	Sickness Impact Profile (SIP subscales mobility control and mobility range, social behavior) [36]

***ICF: participation***	
Limitations in participation and autonomy Quality of life Fall incidence	The Impact on Participation and Autonomy Questionnaire (IPAQ)[37]
	36-Item Short-Form Health Survey (SF-36) [38]
	Telephone computer (weekly calls)**

***ICF: personal factors***	
Coping	Coping Inventory for Stressful Situation (CISS) [30]
	ALCOS-16 [39]
Illness cognitions	Ziekte cognitie lijst (ZCL) [40]
Concentration problems	Checklist Individual Strength (CIS subscale concentration) [21]
Motivation	Checklist Individual Strength (CIS subscale motivation)[21]

***ICF: environmental factors***	
Caregiver strain	Caregiver Strain Index of partner/caregiver (CSI) [41]
Experienced fatigue of patient	Checklist Individual Strength (CIS subscale fatigue, filled in by
from perspective of relative.	relative about patient) [21]
Experienced fatigue of partner.	Checklist Individual Strength (CIS subscale fatigue, filled in by relative about him/herself) [21]
Social support	Sociale steunlijst-subschaal discrepantie (SSL-D verkort) [42]
Coping of partner	Coping Inventory for Stressful Situations (CISS) [30]

*Measured only at inclusion. **Participants will be called weekly throughout the study by a telephone-computer to obtain fall incidence; in the case of fall incident(s), a subsequent telephone interview is held to obtain information about the cause and circumstances of falling, fall direction, possible injury and ability to get up from the floor. ***In all groups, three extra urine samples will be obtained at week 4, 8 and 12 of the intervention period.

At the level of bodily functions and structures, patients are asked to give separate consent for several 'invasive' assessments at baseline and after the intervention period. Blood and urine samples are collected by experienced nurses and will be explored by nuclear magnetic resonance (NMR) for possible biomarkers of disease and response to the interventions. Ultrasound measurements of the thigh muscles are made by an experienced ultrasound professional, blinded for the treatment allocation, and analyzed for muscle thickness and echo intensity. In addition, Magnetic Resonance Imaging (MRI) and ^31^P and proton (^1^H) Magnetic Resonance Spectroscopy (MRS) are performed by trained professionals, blinded for the assignment to the intervention. It has been shown that in vivo MRS is able to produce spectra of multiple metabolites simultaneously and is well suited to study energy metabolism in patients with muscular dystrophies [28,29]. The MR examinations start with T1 and T2 weighted images of the thigh for detailed structural analysis. Muscle involvement is specifically assessed by the presence of fatty infiltration on T1 weighted MR images. ^1^H MRS is used to assess muscle specific creatine as well as extramyocellular lipids and intramyocellular lipids levels, whereas ^31^P MRS is applied to get information about tissue pH and the level of high energy phosphates present in the different thigh muscles.

#### Adverse events

An adverse event is defined as any undesirable experience or outcome. Specially assigned site investigators are instructed to report all adverse events immediately to the primary investigator (NV) and to evaluate each event for its date of onset, possible relation to the interventions (based on clinical judgment), possible treatment and course in time. In addition, adverse events can be reported by the participants directly to the primary investigator and physician (NV). All adverse events reported will be carefully monitored and registered until they have abated or a stable situation has been reached.

#### Statistical Analysis

Generalized estimated equations analysis will be used to investigate differences in the effects on primary and secondary outcome measures between the study groups and to investigate the influence of possible effect modifiers. When necessary, analyses will be adjusted for group differences in fatigue severity and physical activity at baseline. Data will be analyzed according to the intention-to-treat principle.

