### Randomization and blinding

Participants fulfilling all inclusion and exclusion criteria are randomised to one of three groups by creating computer-generated 'blocks' ensuring that the same number of participants is allocated to each group. Experimental group 1 (E1) receives AET and usual care for 3 times a week during 16 weeks. Experimental group 2 (E2) receives CBT and usual care once time a week during 16 weeks. Thereafter, both groups are followed up for 6 months. A third group (C) receives usual care only for 16 weeks and serves as a waiting list control group. After another 3-months follow-up (i.e. 7 months after inclusion), this group will as yet be randomised to either AET or CBT for 16 weeks and followed up until 6 months later (total time in study 17 months) (figure 2). All outcomes are assessed by blinded and independent physical therapists. At the beginning of each assessment, patients are always instructed not to reveal their group allocation to the blinded assessor.

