#### Power

In order to detect a 10% group difference (E1 and E2 versus C) in change in fatigue severity between the start and the end of the intervention period (assuming difference in standard deviation between the start and the end of the intervention (SDdif) = 10%, α = .05, β = .80), 20 participants per group are required. With an expected drop-out rate of maximally 25%, 25 participants will be recruited in each group (n = 75).

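### GEE is the only model named for about 19-25 patients per group: uncorrected, its tests are mildly too liberal, and its protection against drop-out depends on the working correlation

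*Protocol article*

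**What the plan says.** The Statistical Analysis section of the protocol article fixes one method for all outcomes: "Generalized estimated equations analysis will be used to investigate differences in the effects on primary and secondary outcome measures between the study groups". The same method is to serve for effect modifiers. Two further statements follow: "When necessary, analyses will be adjusted for group differences in fatigue severity and physical activity at baseline" and "Data will be analyzed according to the intention-to-treat principle". The section does not give a variance estimator, a reference distribution, a working correlation or a missing-data assumption.

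The size is set in the Power section: "In order to detect a 10% group difference (E1 and E2 versus C) in change in fatigue severity", with 20 per group required, and then "With an expected drop-out rate of maximally 25%, 25 participants will be recruited in each group (n = 75". Allocation is equal over three groups (Randomization and blinding: "ensuring that the same number of participants is allocated to each group").

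Outcome assessment sets visits at T0, T1 (end of the 16 weeks), T2 (3 months of follow-up) and T3 (6 months). Compliance and attrition says that patients who stop therapy are urged to keep attending assessments. Randomization and blinding says that the control group is randomised to one of the active treatments about 7 months after inclusion.

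**The concern.** The sandwich variance usually reported with GEE is a large-sample estimator. It uses squared residuals from fitted means, and with few patients per group those residuals are too small on average. The z or chi-square reference then ignores the uncertainty in the variance itself. Both errors make p-values too small, and they add up when several coefficients are tested jointly.

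A separate point concerns drop-out. Unweighted GEE has no general guarantee when drop-out depends on earlier observed outcomes. Such drop-out is plausible here: every patient is severely fatigued at entry, and one arm trains three times a week for 16 weeks. At stake are the error rate and, under some choices, the bias of the comparison on the primary outcome, CIS-fatigue.

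**Working it through.** **Group size.** The Power section gives a difference of 10%, an SD of change of 10%, α = 0.05 and, reading its β = .80 as power, power 0.80.
- Two-sided, two equal groups: n = 2(1.96 + 0.84)² × (10/10)² ≈ 15.7, so 16 per group (17 with the t distribution). The stated 20 is not reproduced, but it errs on the large side. That is a separate matter and does not affect this point.
- Drop-out: 20 × 1.25 = 25 recruited, and 25 × 0.75 = 18.75 remaining. So about 19 to 25 per group, or 56 to 75 in total, are analysed.

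**Single contrast, by formula.** Take complete data, normal outcomes and a saturated group-by-visit model. The sandwich SE for one active group against control, in change from T0 to T1, is then the pooled SE times √((n−1)/n). The uncorrected z test therefore has type I error P(|t with 2n−2 df| > 1.96 × √((n−1)/n)).

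| n per group | √((n−1)/n) | SE too small by | Cut-off | Type I error |
|---|---|---|---|---|
| 19 | 0.973 | 2.7% | 1.908 | 6.4% |
| 20 | 0.975 | 2.5% | 1.910 | 6.4% |
| 25 | 0.980 | 2.0% | 1.920 | 6.1% |

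This result does not depend on the correlation between visits.

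**Single contrast, by simulation.** Assumptions, none of them from the article: three groups, T0-T2, SD 10, exchangeable correlation 0.5, no true effect. The SD of change is 10 × √(2 × (1 − 0.5)) = 10, which matches the standardised difference of 1 in the Power section. Runs numbered 1,500 or 3,000, with a Monte Carlo SE of about 0.4-0.6 points.

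| Per group, drop-out | Working correlation | Bias | Sandwich, z | Mancl-DeRouen, z | Mancl-DeRouen, t |
|---|---|---|---|---|---|
| 19, none | exchangeable | 0.03 | 5.8% | 4.9% | 4.3% |
| 19, none | independence | −0.08 | 6.9% | 5.3% | 4.7% |
| 25, none | exchangeable | −0.01 | 5.8% | 5.1% | 4.5% |
| 25, about 25% completely at random | independence | 0.00 | 6.0% | 4.7% | 4.3% |
| 25, about 25% completely at random | exchangeable | −0.02 | 6.1% | 5.3% | 4.9% |
| 25, missing at random | independence | −1.92 | 10.4% | 9.0% | 8.4% |
| 25, missing at random | exchangeable | −0.16 | 5.6% | 4.8% | 4.5% |

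With complete data the two working correlations give the same estimate and the same sandwich in this model. The gap between 5.8% and 6.9% at 19 per group is therefore simulation noise around the 6.4% from the formula.

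**Missing-at-random scenario.** The log-odds of leaving after a visit were −2.25 ± 1.5 × (fatigue at that visit in SD units). The worse patients left the active groups and the better ones left control. This is deliberately severe. Bias under independence is 1.92/10 = 0.19 SD, and under exchangeable 0.16/10 = 0.02 SD.

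**Joint group-by-time Wald test.** The degrees of freedom are 2 × 1 = 2 over T0-T1 and 2 × 2 = 4 over T0-T2. Two separate sets of null simulations (2,500 and 3,000 runs, correlation 0.5) gave:
- T0-T1, 20 per group: 7.6% and 7.9%.
- T0-T1, 25 per group, 25% random drop-out: 7.7% (one set only).
- T0-T2, 25 per group, 25% random drop-out: 9.6% and 9.1%.

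**The case against.** The strongest reply is that the article names GEE and no more. It does not say that the sandwich will be uncorrected or the working correlation independence. A condensed article commonly leaves such details to the full protocol or analysis plan, and GEE with a corrected variance would fit its wording exactly. This stands. A reader might infer that the trial's intervals and p-values are too favourable, but the document supports only the conditional statement that they would be if the usual default were used.

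Second, the Power section points to the change over the intervention period, and for that contrast the excess is only 1 to 1.5 points. No joint test is specified. This also stands, so the 7-10% applies only if such a test is used. The corrected version with a t reference came out at 4.2-5.1% across the simulations under random or no drop-out, so it may be slightly conservative.

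Third, a reader might infer that GEE needs drop-out to be completely at random. That is too strong. With a continuous outcome and a correct working correlation, the bias nearly vanished even in the severe scenario. The 25% is also an upper limit, and stopping therapy need not mean a missing outcome.

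Fourth, a still larger inflation could be computed for a three-group test over T0-T3. The design does not support it: controls move to active treatment about 7 months after inclusion, so there is no untreated control at T3.

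What remains is that a method, a sample size and a drop-out allowance are all stated, and a better-calibrated method for that combination is readily available.

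**Conclusion.** The point holds in a limited form, as a cheap improvement and not as an error that undermines the trial. With 19-25 patients per group, uncorrected GEE has a type I error of about 6-6.5% on the single T0-T1 contrast. It has about 7-10% on a joint group-by-time test over T0-T1 or T0-T2. The single-contrast figure rests on normality and complete data. The joint-test figures also rest on an assumed correlation of 0.5.

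The drop-out risk depends on a choice that the article does not state. In one severe, assumed scenario the bias was 0.19 SD under independence and 0.02 SD under a correct exchangeable structure. A corrected standard error does not cure that bias: under independence the error rate stayed at 8.4-9.0%.

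**What to change.** For CIS-fatigue and the other continuous outcomes, replace GEE by a mixed model for repeated measures. Fit it by REML with group, visit and their interaction, an unstructured covariance, baseline as a covariate in every case, and Kenward-Roger degrees of freedom. Restrict the three-group comparison to T1 and T2. This model is valid under missing at random without relying on a well-chosen working correlation.

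If GEE is kept, or is needed for outcomes such as fall counts, state three things: a working correlation other than independence, a small-sample corrected sandwich such as Mancl-DeRouen, and a t or F reference.

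The cost is analysis wording and standard software; no visit, patient or procedure changes. Intervals become slightly wider. In the simulations the corrected SE was 3.31 against 3.13 at 19 per group (3.31/3.13 = 1.06) and 2.87 against 2.75 at 25 per group (2.87/2.75 = 1.04). That is about 4-6%, plus a little for the t multiplier.

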## Methods

### Study population

It is intended to include 75 FSHD patients, diagnosed on both clinical and genetic grounds, aged 18 years and older. All patients who participated in previous FSHD studies at the Radboud University Nijmegen Medical Centre [10,12,14,18] are approached by the primary investigator (NV). In addition, all patients known at the departments of Neurology and Rehabilitation of the Radboud University Nijmegen Medical Centre, University Medical Centre of Utrecht, Amsterdam University Medical Centre or any of the affiliated rehabilitation centres are invited to participate as well. In addition, patients who are registered in the Dutch neuromuscular "computer registry of all myopathies and polyneuropathies" (CRAMP) database [19] and/or who are member of the Dutch patient support organisation "vereniging spierziekten Nederland" (VSN) will be invited by the primary investigator (NV) and a member of the VSN, respectively, to take part in the study. If the patient is willing to participate, the primary investigator (NV) will check the inclusion and exclusion criteria (table 1) and estimate the disease severity using the Ricci score [20]. When a patient meets all the criteria, oral and written informed consent are obtained according to the declaration of Helsinki. Separate consent is asked to (i) obtain blood and urine samples, and/or (ii) undergo magnetic resonance imaging (MRI)/spectroscopy (MRS), and/or (iii) undergo muscle ultrasound. The study protocol was approved by the Dutch ethical committee CCMO (Centrale commissie mensgebonden onderzoek) and all participating centers granted (ethical) approval to participate.

**Table 1 T1:** Inclusion and exclusion criteria

Inclusion criteria
(1) age 18 years and older

(2) suffering from severe fatigue (CIS-fatigue ≥ 35) [21]

(3) ability to walk independently (ankle-foot orthoses and canes are accepted)

(4) being able to exercise on a bicycle ergometer

(5) being able to complete either type of intervention

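### Baseline CIS-fatigue is adjusted for only if the groups are seen to differ, which leaves the primary model open and gives up some precision

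*Protocol article*

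**What the plan says.** The Statistical Analysis section names the method: "Generalized estimated equations analysis will be used to investigate differences in the effects on primary and secondary outcome measures between the study groups". It then gives the rule for covariates: "When necessary, analyses will be adjusted for group differences in fatigue severity and physical activity at baseline". It does not say what makes adjustment necessary, and no other section of the article fixes the covariates.

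One of the two conditional covariates is the baseline of the primary endpoint itself. Under Outcome assessment, "The primary outcome measure is fatigue severity as assessed with the CIS-fatigue", and it is measured at T0 as well as at T1, T2 and T3. Every participant has a screening value, because Table 1 requires "suffering from severe fatigue (CIS-fatigue ≥ 35" or more.

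The Power section is framed on the "change in fatigue severity between the start and the end of the intervention period" and mentions no baseline adjustment.

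**The concern.** Participants are allocated by computer-generated blocks, so any baseline difference between groups is chance. The size of that difference in one trial is a poor guide to whether a covariate belongs in the model. Baseline CIS-fatigue is worth including because it is expected to predict later CIS-fatigue, and that is so whether or not the groups happen to differ.

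Two things are at stake.

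- **The primary model is not fixed.** An unadjusted analysis, one adjusted for CIS-fatigue and one adjusted for CIS-fatigue plus physical activity all fit the sentence. With no criterion, the choice can be made after the results of each are known.
- **Precision is given up.** If the groups look alike, the rule leaves out a prognostic covariate that is already collected.

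This is not a detail left to an analysis plan that is not shown. The article states a rule that depends on the data, and a plan that fixed the covariates would have to depart from it.

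**Working it through.** **1. The plan's own figure.** The Power section aims "In order to detect a 10% group difference (E1 and E2 versus C) in change in fatigue severity", with inputs printed as "SDdif) = 10%, α = .05, β = .80". I read .80 as power and assume a two-sided test. Then n = 2 × (1.960 + 0.842)² × (10/10)² = 15.7, so 16 per group (17 with the t distribution), against the stated 20. That mismatch is a separate matter. At 20 per group, an unadjusted change score has power Φ(10/(10 × √(2/20)) − 1.960) = Φ(3.162 − 1.960) = 0.885 (0.869 with t).

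**2. Inputs for precision.**
- 20 per group (Power).
- Entry limited to the top 61% of the source population, since the Background reports that 61% of FSHD patients score 35 or more.
- T0-T1 correlation ρ before selection: 0.3, 0.5 or 0.7. This is an assumption.
- Normal scores with variance 1 before selection.

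**3. Variance of baseline after selection.** The cut-off is z = −0.279, with density 0.384, so λ = 0.384/0.61 = 0.629. The variance is v = 1 + (−0.279)(0.629) − 0.629² ≈ 0.43.

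**4. Adjusted against change-score variance.** The variance of change is (1−ρ)²v + (1−ρ²), and the residual variance after adjustment is 1−ρ². Estimating the slope with 40 participants multiplies the latter by about 1 + 1/36.

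| ρ | (1−ρ²) / [(1−ρ)²v + 1−ρ²] | × (1 + 1/36) | simulated |
|---|---|---|---|
| 0.3 | 0.91/(0.21+0.91) = 0.81 | 0.84 | 0.84 |
| 0.5 | 0.75/(0.107+0.75) = 0.87 | 0.90 | 0.90 |
| 0.7 | 0.51/(0.039+0.51) = 0.93 | 0.96 | 0.95 |

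Without the entry threshold, the ratio would be (1+ρ)/2 = 0.65, 0.75 or 0.85. The threshold narrows the baseline range and so reduces the gain.

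**5. What that is worth.** With the SD of change held at 10%, power at 20 per group is Φ(3.162/√ratio − 1.960). For ratios 0.84, 0.90 and 0.95 this gives Φ(1.490) = 0.93, Φ(1.373) = 0.92 and Φ(1.284) = 0.90, against 0.885 unadjusted. Equivalently, 20 adjusted participants do the work of 20/0.84 = 23.8, 20/0.90 = 22.2 or 20/0.95 = 21.1 unadjusted ones.

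**6. Type I error, simulated with truncated baselines and 20 per group.**

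| Procedure | Type I error |
|---|---|
| Change score always | 4.9-5.1% |
| Fixed rule: adjust if baseline p<0.05 | 4.5-5.0% |
| Better of two (change score, CIS-adjusted) | about 6-7% |
| Best of three (also CIS plus activity) | about 7-8.5% |

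The three-model row also assumes that activity correlates 0.3 with the outcome residual. Without truncation, and with either a change score or a follow-up score as the unadjusted analysis, the fixed rule gives 3.6-4.9% and the better of two gives 6.5-8.0%.

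**7. A p<0.05 trigger seldom fires.** By construction it leads to adjustment in about 5% of trials, so such a rule recovers almost none of the available precision.

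**The case against.** The strongest defence is that the harm is limited. The unadjusted comparison is unbiased over repeated randomisation, only two covariates are named, and power at 20 per group already exceeds 0.80 on the stated inputs. The model is a GEE. If T0 enters as a response with a common baseline mean, precision is already close to that of an adjusted analysis, and an article commonly leaves that detail to a fuller document. All of this stands and limits the size of the point. It does not supply a criterion for adjusting.

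Three stronger readings are tempting, and the documents do not support them.

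- **The rule itself inflates the type I error.** It does not if the trigger is fixed in advance (step 6). The 6-8.5% figures describe an analyst who takes the most favourable result. The article does not say that this will happen; it only fails to exclude it.
- **The entry threshold of 35 biases an unadjusted change score through regression to the mean.** The threshold applies to every arm before randomisation, so expected regression is equal and cancels between groups. The simulated mean difference under the null is about zero.
- **An unadjusted change score misleads when the groups clearly differ at baseline.** That is when the rule would adjust. In those trials the adjusted test rejects a true null about 4-6% of the time.

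**Conclusion.** The point holds in a limited form and is a should-fix. The article makes adjustment for the primary outcome's own baseline depend on observed group differences, with no criterion, so the primary model is not settled before the data are seen.

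The size is modest. At worst, type I error is about 6-7% with two candidate models and 7-8.5% with three, and only under free choice. Leaving the baseline out forgoes about 16%, 10% or 5% of the change-score variance at ρ = 0.3, 0.5 or 0.7. These figures rest on an assumed correlation, normal scores, the 61% truncation and a change-score comparator taken from the Power section. The precision loss is smaller if the GEE constrains the baseline means to be equal. The lack of a fixed primary model does not depend on any of these assumptions. Nothing here shows that the trial is biased or underpowered.

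**What to change.** Replace the conditional sentence by:

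> The comparison of CIS-fatigue is always adjusted for baseline (T0) CIS-fatigue, regardless of observed group differences; secondary outcomes that are measured at baseline and at follow-up are adjusted for their own baseline value. Baseline physical activity is either always included in the primary model or used only in a sensitivity analysis, decided before the data are seen.

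The clause on secondary outcomes is restricted on purpose. Fall incidence is collected by weekly calls during the study, with no baseline count described, and the footnote to Table 2 says that blood pressure is measured only at inclusion.

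The cost is one sentence and one degree of freedom in the primary model, or two if physical activity is always included. No new data are needed.

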**Methods/Design:**

A multi-centre, assessor-blinded, randomized controlled trial is conducted. A sample of 75 FSHD patients with severe chronic fatigue (CIS-fatigue ≥ 35) will be recruited and randomized to one of three groups: (1) AET + usual care, (2) CBT + usual care or (3) usual care alone, which consists of no therapy at all or occasional (conventional) physical therapy. After an intervention period of 16 weeks and a follow-up of 3 months, the third (control) group will as yet be randomized to either AET or CBT (approximately 7 months after inclusion). Outcomes will be assessed at baseline, immediately post intervention and at 3 and 6 months follow up.

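### The only covariates named for adjustment are baseline fatigue and physical activity; for most secondary outcomes the plan does not provide for the outcome's own T0 value

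*Protocol article*

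**What the plan says.** Protocol article, Statistical Analysis: "Generalized estimated equations analysis will be used" to investigate "differences in the effects on primary and secondary outcome measures between the study groups". One sentence then deals with covariates. It opens with a condition, "When necessary, analyses will be adjusted for group differences", and names two baseline variables: the analyses are to be "adjusted for group differences in fatigue severity and physical activity at baseline". No criterion is given for when adjustment is necessary, and no outcome's own baseline is mentioned.

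The T0 values exist. The abstract states: "Outcomes will be assessed at baseline, immediately post intervention and at 3 and 6 months follow up". The Outcome assessment section adds: "The baseline (T0) and post treatment (T1) visits consist of muscle strength testing of the thigh and aerobic exercise tolerance testing", together with questionnaires and the actometer.

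The Power section frames the primary effect as a group difference "in change in fatigue severity between the start and the end of the intervention period". No power or sample size is given for any secondary outcome.

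**The concern.** The two named covariates suit the primary outcome: baseline fatigue severity is the own baseline of CIS-fatigue. They are then carried over unchanged to outcomes they predict less well. For VO2max, quadriceps strength or caregiver strain, the strongest baseline predictor is normally the same measure at T0.

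The trigger does not help either. It responds to group differences in fatigue and activity. If the groups differ at T0 in strength but are alike in fatigue and activity, nothing in the sentence calls for adjustment, and adjusting for the two named variables would correct little of the difference.

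What is at stake is the information from the secondary objectives. These span all levels of the International Classification of Functioning and rest on 25 recruited patients per group, or about 19 after the allowed loss (25 × 0.75 = 18.75). In groups of this size, T0 imbalances are common and precision is scarce.

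**Working it through.** **Plan's own figure.** The plan gives none for secondary outcomes. Its 20 per group concerns the primary outcome only and is used here just as a group size.

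**Inputs.** From the Power section: 20 evaluable and 25 recruited per group. Assumed, because the documents do not give it: the correlation r between an outcome's T0 and follow-up value, taken as 0.5 to 0.9, with equal SD at both times.

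**Variance factors** (the variance of a two-group difference is 2f/n, in units of the outcome's SD squared):

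- follow-up value only: f = 1
- difference in change, which is what a GEE with T0 as a response and free group-by-visit terms estimates: f = 2(1 − r)
- adjusted for own T0: f = 1 − r²

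Against the change contrast, the ratio is (1 − r²)/[2(1 − r)] = (1 + r)/2, so own-T0 adjustment removes (1 − r)/2 of the variance. Against follow-up only, it removes r².

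| r | change | own T0 | removed vs change | removed vs follow-up only |
|---|---|---|---|---|
| 0.5 | 1.00 | 0.75 | 25% | 25% |
| 0.7 | 0.60 | 0.51 | 15% | 49% |
| 0.9 | 0.20 | 0.19 | 5% | 81% |

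Against the change contrast, the standard error falls by 1 − √0.75 = 13%, 1 − √0.85 = 8% and 1 − √0.95 = 2.5%. Put the other way, the change contrast has a variance 1/0.75, 1/0.85 or 1/0.95 times what is needed: 33%, 18% or 5% higher. At r = 0.7 the gain is worth 25/0.85 = 29.4, about 4 extra patients per group.

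**Detectable difference** at 80% power, two-sided 0.05, 20 per group, 2.80 × √(2f/20):

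- r = 0.5: 0.89 SD for change, 0.77 SD with own T0
- r = 0.7: 0.69 SD for change, 0.63 SD with own T0

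**Chance imbalance.** With 25 per group, the SD of a T0 difference between two groups is √(2/25) = 0.28 SD. The probability of a difference above 0.3 SD is 0.29, and above 0.5 SD it is 0.08, per measure and pair of groups.

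**Simulation check.** 4,000 two-group trials were simulated with 20 per group. The two other covariates each correlated 0.2 or 0.4 with the outcome's T0 value, r times that with follow-up, and 0.3 with each other. The share of a T0 imbalance carried into the estimate, for r = 0.5 to 0.7, was:

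- follow-up only: 0.48 to 0.69
- follow-up plus the two other covariates: 0.38 to 0.64
- difference in change: −0.52 to −0.31 (over-correction; theory gives −(1 − r))
- own T0: about 0

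Standard errors at r = 0.7 and covariate correlation 0.4 were 0.318 for follow-up only, 0.304 with the two covariates, 0.246 for change and 0.227 with own T0. The two covariates recover little of what own T0 gives.

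**The named covariates under the change reading.** With complete data and an independence or exchangeable working correlation, covariates that are constant over time and enter as main effects leave the group-by-visit contrast unchanged. Adjusting for baseline fatigue and activity in that way would do essentially nothing for the contrast of interest.

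**The case against.** The strongest reply is that this is a three-sentence section in a condensed article. It does not call its covariates exhaustive, and how T0 enters each model is a detail that a statistical analysis plan, not shown here, may settle. Not named is not the same as not used. This stands as a limit on the claim: if own T0 is already a covariate in each model, nothing is lost. It does not remove the point, because the article does not leave covariates open. It names two for all outcomes, and they fit most secondary outcomes poorly.

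Several stronger readings are tempting and are not supported:

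- A reader might infer that T0 is ignored. With follow-up values only and covariates unrelated to the outcome, the standard error would be 1/√(1 − r²) times as large as with own T0: 15%, 40% or 129% larger at r = 0.5, 0.7 or 0.9. Repeated measurement from T0 and a power statement on change make this the least likely reading.
- A reader might infer that the two covariates are fixed for every model. The adjustment is conditional.
- A reader might infer that every secondary measure is affected. Table 2 marks blood pressure as measured only at inclusion. Falls are counted by weekly calls, with no T0 score described. For the physical-activity measures, a named covariate may be the own baseline.
- A reader might infer bias, or harm to the primary result. Randomisation keeps the estimates unbiased on average, and the own baseline of CIS-fatigue is among the named covariates.

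A GEE with free group-by-visit terms is also a valid analysis. The argument against it here is one of efficiency and of conditional imbalance.

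**Conclusion.** The point holds in limited form. For most secondary outcomes with a T0 and a follow-up value, the stated adjustment does not provide for the own baseline, and the two named covariates do not replace it.

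On the reading closest to the Power section's change measure, 5% to 25% of the variance is avoidable for r from 0.9 to 0.5, and a chance T0 imbalance is over-corrected by a fraction 1 − r. If T0 is unused, the loss is equal at r = 0.5 and larger above it. If own T0 is already a covariate, it is zero. These sizes rest on assumed correlations, equal SDs at T0 and follow-up, and complete data. No figure in the article changes. The point is worth correcting because the gain costs almost nothing and the groups are small.

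**What to change.** Add one sentence to the analysis section: in the model for each secondary outcome that has a T0 value, that outcome's own T0 value is a covariate, fixed in advance and regardless of observed imbalance. Baseline fatigue and physical activity may stay as additional covariates.

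An alternative is a longitudinal model with T0 among the responses and a common T0 mean across groups. In a GEE this needs a working correlation other than independence, because under independence the constraint leads back to the follow-up-only estimate.

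The cost is one degree of freedom per model and no new data. Outcomes without a T0 value, such as falls, are analysed without it.
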